The present study introduces HMA, an integrative protocol designed to address both physical and emotional symptoms associated with nicotine withdrawal. HMA integrates traditional meridian theory with neurofunctional acupuncture point selection to target craving, emotional dysregulation, and autonomic imbalance. This pragmatic randomized controlled trial aims to evaluate the effectiveness and safety of HMA in combination with NRT in individuals with TUD under real-world clinical conditions. The primary objective is to evaluate the effect of HMA plus NRT on nicotine craving reduction; secondary outcomes assess abstinence rates and psychological measures. HMA employs a multidomain acupuncture point strategy intended to influence central neural processes, stabilize emotional responses, and support physiological regulation. This integrative approach is designed to address multiple components of nicotine withdrawal that may not be fully targeted by pharmacotherapy alone. Although evidence for acupuncture in substance dependence remains mixed, particularly for auricular approaches, emerging studies suggest that body- and scalp-based protocols targeting prefrontal–limbic circuitry may be associated with reductions in craving and improvements in affective symptoms. This pragmatic trial is expected to contribute to the existing evidence base by evaluating a standardized, symptom-oriented acupuncture protocol in combination with NRT in a clinically relevant setting.

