The sample size was calculated based on the co-primary outcome of 7-day point prevalence abstinence (PPA) at week 6. Referring to recent systematic reviews of acupuncture smoking cessation trials (21, 22), a control group abstinence rate of approximately 15% was assumed, with an odds ratio (OR) of 1.9 for the HMA + NRT group. With a two-sided significance level of *α* = 0.05, 80% power, and a 1:1 allocation ratio, a total of 188 participants is required. Accounting for a 15% dropout rate, the final sample size is set at 220 participants (110 per group) (23). The VAS craving outcome, as the other co-primary endpoint, is also adequately powered based on the same sample size. Multiplicity control. Because two co-primary outcomes are designated, the overall type I error rate is controlled using the Hochberg procedure. Under this approach, each outcome is tested at the full *α* = 0.05 level; the family-wise error rate is preserved because the trial is considered positive only if both co-primary outcomes achieve statistical significance (*p* ≤ 0.05 each). This method offers greater power than Bonferroni correction while maintaining strong control of the family-wise error rate.

To monitor expectancy and attention effects, participants will complete the Credibility/Expectancy Questionnaire (CEQ) at baseline and post-randomization; these scores will be explored in sensitivity analyses (16).

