#### Two co-primary outcomes will be analyzed as follows

2.10.1

Multiplicity control for co-primary outcomes. Type I error is controlled at the family-wise level using the Hochberg procedure. The trial will be declared positive only if both co-primary outcomes (VAS craving change and PPA at week 6) achieve statistical significance at *p* ≤ 0.05.

The change in nicotine craving intensity measured by the VAS from baseline to week 6 (one of the two co-primary outcomes) will be analyzed using linear mixed-effects models including fixed effects for group, time, and group × time interaction, with participant-specific random intercepts to account for repeated measurements.

The PPA at week 6 (the second co-primary outcome) will be analyzed using generalized estimating equations (GEE) with a logit link function and an exchangeable correlation structure. Results will be reported as adjusted odds ratios (ORs) with 95% confidence intervals (CIs).

For smoking abstinence outcomes, missing smoking-status data will be treated as non-abstinent in the primary analysis. For sensitivity analysis, a pattern mixture model under missing-not-at-random (MNAR) assumptions will be applied, assuming a relapse rate of 80–90% among participants with missing follow-up data (42).

Secondary continuous outcomes will be analyzed using linear mixed-effects models, including fixed effects for group, time, and group × time interaction, and random intercepts to account for within-subject correlation. Models will be adjusted for baseline values where appropriate. SF-36 total scores and PSQI global scores will be analyzed directly, with similar models applied to BDI-II, BAI, and exhaled carbon monoxide (CO).

To control for type I error due to multiple comparisons across the secondary outcomes (BDI-II, BAI, SF-36, PSQI, CO), a false discovery rate (FDR) procedure will be applied. Adjusted *p*-values will be reported alongside unadjusted estimates, and findings will be interpreted with appropriate caution (43).

Prespecified subgroup analyses will include three-way interaction terms (subgroup × treatment × time) within mixed-effects models to explore potential effect modification by sex (male/female) and age (<40 vs. ≥40 years).

Sensitivity analyses will include a per-protocol (PP) analysis excluding participants with less than 80% adherence, defined as attendance at fewer than 14 of 18 acupuncture sessions or NRT use on fewer than 80% of study days.

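### The multiplicity method is named Hochberg, but the rule adopted is a both-must-win (intersection-union) test; the justification does not fit the name and the power cost is not stated

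*Protocol article*

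**What the plan says.** Section 2.3 states that "the overall type I error rate is controlled using the Hochberg procedure", that under this approach "each outcome is tested at the full *α* = 0.05 level", and that "the family-wise error rate is preserved because the trial is considered positive only if both co-primary outcomes achieve statistical significance". It adds: "This method offers greater power than Bonferroni correction while maintaining strong control of the family-wise error rate".

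Section 2.10.1 repeats the label, "Type I error is controlled at the family-wise level using the Hochberg procedure", and then the success rule: "The trial will be declared positive only if both co-primary outcomes (VAS craving change and PPA at week 6) achieve statistical significance". The threshold for each outcome is 0.05.

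The sample size in 2.3 rests on PPA alone: "With a two-sided significance level of *α* = 0.05, 80% power, and a 1:1 allocation ratio", with 15% control abstinence and an odds ratio of 1.9, giving 188 before dropout and 220 after it. For VAS the section asserts adequate power at the same size but gives no difference, standard deviation or power. Section 3.1 (Limitations) says the sample is large enough for both outcomes.

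The Introduction ranks the outcomes differently: "The primary objective is to evaluate the effect of HMA plus NRT on nicotine craving reduction; secondary outcomes assess abstinence rates and psychological measures". The Abstract, Table 1, 2.6.1 and 2.10.1 all make PPA co-primary.

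**The concern.** With two hypotheses, Hochberg rejects both if the larger p is at most 0.05. Otherwise it rejects the hypothesis with the smaller p if that p is at most 0.025. It is designed to permit a claim on either outcome. A rule that tests each outcome at 0.05 and requires both to succeed is an intersection-union test. It needs no multiplicity adjustment, and its price is power. The protocol names the first method and defends it with the reasoning of the second.

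The practical stake is the split result. Suppose VAS gives p = 0.01 and PPA gives p = 0.20. By the stated success rule the trial is not positive. An author who relies on the word Hochberg could still report the craving effect as confirmed with error control. VAS is self-reported by participants who know their allocation, and section 3.1 explains that PPA was made co-primary partly to offset that weakness. The comparison with Bonferroni also draws attention away from the power that a both-must-win rule gives up.

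**Working it through.** **Inputs.** From 2.3: two-sided alpha 0.05, 80% power for PPA, control rate 15%, OR 1.9, 188 in total (94 per arm), 220 after 15% dropout (110 per arm). Assumed, because the protocol gives neither: VAS power of 80–95%, and a correlation of 0 to 0.5 between the two test statistics.

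**The plan's own figure.** The odds in the HMA + NRT arm are 1.9 × 0.15/0.85 = 0.3353, so the rate is 0.3353/1.3353 = 25.1%. The usual two-proportion formula then needs 492 in total for 80% power. Unpooled, log-odds-ratio, arcsine, continuity-corrected and one-sided variants, and reading 1.9 as a risk ratio, give 230 to 530. None gives 188. That is a separate matter, but it sets the PPA power used here. The dropout step is acceptable (188/0.85 ≈ 221; 220 stated).

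PPA power at 94 per arm: the difference is 0.1011, the null SE 0.0584 and the alternative SE 0.0579. Then Φ[(0.1011 − 1.96 × 0.0584)/0.0579] = Φ(−0.23) = 41%. At 110 per arm it is 46%.

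**Formulas, independent outcomes.** A test with 80% power at 0.05 has a mean z of 1.960 + 0.842 = 2.802. Its power at 0.025 is therefore Φ(2.802 − 2.241) = 0.712.

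Both outcomes at 80%:
- Both p ≤ 0.05: 0.80 × 0.80 = 0.64.
- Hochberg rejects exactly one: 2 × 0.712 × 0.20 = 0.285.
- Hochberg, at least one: 0.64 + 0.285 = 0.925.
- Bonferroni, at least one: 1 − 0.288² = 0.917.
- Both p ≤ 0.025: 0.712² = 0.507.

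PPA at 41% (30.3% at level 0.025) with VAS at 80%:
- Both p ≤ 0.05: 0.409 × 0.80 = 0.327.
- Hochberg rejects exactly one: 0.712 × 0.591 + 0.303 × 0.20 = 0.482.

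**With correlation.** Simulation used 2,000,000 bivariate-normal pairs per scenario. Each range runs from correlation 0 to correlation 0.5.

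| PPA power | VAS power (assumed) | Both p ≤ 0.05 | Hochberg rejects at least one, both-must-win fails |
|---|---|---|---|
| 80% (stated) | 80% | 64% to 69% | 29% to 18% |
| 80% (stated) | 90% | 72% to 75% | 24% to 16% |
| 41% (94 per arm) | 80% | 33% to 38% | 48% to 37% |
| 41% (94 per arm) | 90% | 37% to 40% | 53% to 46% |
| 41% (94 per arm) | 95% | 39% to 40% | 56% to 52% |
| 46% (110 per arm) | 80% | 37% to 43% | 45% to 34% |
| 46% (110 per arm) | 90% | 42% to 45% | 49% to 41% |
| 46% (110 per arm) | 95% | 44% to 46% | 51% to 46% |

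If VAS power were only 50%, the last column would be 31–43% at the stated PPA power and 23–39% at the recomputed PPA power.

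**Type I error.** With no effect on either outcome (correlation 0 to 0.8), both-must-win is positive in 0.25% to 2.2% of trials, and Hochberg rejects something in 4.4% to 5.0%. With one outcome null and the other powered at 80–90%, both-must-win is positive in 3% to 5%.

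**The case against.** The strongest reply is that the trial verdict is not in doubt. Sections 2.3 and 2.10.1 give the same success condition, no section says that one outcome suffices, and Hochberg's first step coincides with the condition. This stands. A reader might infer that the protocol leaves the success rule open, to be chosen after the data are seen, but the text does not support that. What remains open is narrower: whether one outcome may be claimed as confirmed in a trial already declared not positive.

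A reader might also infer that the two rules part company in about half of trials. That needs the recomputed PPA power together with high assumed VAS power or low correlation. At the protocol's stated PPA power, with VAS at 80–90%, the share is 16–29%. Nor is a split result always the likeliest one. At 80% power for each outcome and independence, success on both (64%) is likeliest. At 41% for PPA and 50% for VAS, failure on both is likeliest (about 41%).

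It is tempting, too, to call the Bonferroni sentence simply false. Compared like with like, it is not. Genuine Hochberg slightly beats Bonferroni for at least one outcome (93% against 92%), and both at 0.05 beats both at 0.025 (64% against 51%). Setting 64% for both against 92% for at least one compares different goals. The sentence still misleads, because an intersection-union test needs no correction, so a gain over Bonferroni is not the relevant comparison and the loss of joint power goes unmentioned.

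Finally, the Introduction might be read as a third multiplicity rule. It is a contradiction in the ranking of outcomes and states no testing rule.

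**Conclusion.** The point holds as an error of naming and justification with an unstated power cost. The rule adopted in 2.3 and 2.10.1 is an intersection-union test, not Hochberg. The two differ on whether one outcome can be claimed alone at p ≤ 0.025. Error control is not lost under either.

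The choice would matter in about 16–29% of trials if PPA has the stated 80% power and VAS 80–90%. It would matter in about 34–56% if PPA has the 41–46% implied by 15% and OR 1.9 and VAS 80–95%. Joint power under the adopted rule is about 64–75% in the first setting and about 33–45% in the second (VAS 80–90%). All these ranges assume a correlation of 0 to 0.5. The VAS power is an assumption throughout. The contradiction itself depends on none of these figures.

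**What to change.** Keep the both-must-win rule, which the protocol already states twice.

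- In 2.3 and 2.10.1, replace the Hochberg label with an intersection-union test, each outcome at two-sided 0.05 without alpha adjustment.
- In 2.3, the only place where it occurs, delete the sentence comparing power with Bonferroni.
- State the joint power with the VAS assumptions behind it, and qualify the statement in 3.1 that the sample is sufficient for both outcomes.
- State that neither outcome will be claimed as confirmed if the other fails.
- In the Introduction, make PPA co-primary.

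If the sponsor does intend Hochberg, remove the both-must-succeed condition from 2.3 and 2.10.1 and write out the 0.05/0.025 step-up rule.

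Either route changes wording only and should be settled before unblinding. Making the text consistent needs no extra patients. The price is that the power the protocol can state becomes less favourable.

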### Interventions

2.4

Acupuncture interventions will be delivered by licensed acupuncturists with at least 3 years of clinical experience. The HMA protocol is based on classical meridian theory and adapted from prior randomized controlled trials, with refinement by a panel of senior experts. All practitioners will undergo standardized training before trial initiation, and a detailed procedural manual will be provided to ensure protocol adherence and minimize inter-operator variability.

Participants in the intervention group will receive HMA in addition to a standardized NRT regimen (identical to the control group). Acupuncture sessions will last approximately 30 min and will be administered three times per week for 6 weeks (total of 18 sessions). The control group will receive NRT alone. Following the treatment phase, participants will enter a follow-up period with assessments at Weeks 10 and 24. The intervention schedule is summarized in Table 1, with detailed acupuncture procedures provided in Tables 2, 3 and Figure 2. All participants will receive standardized brief behavioral counseling consistent with clinical smoking cessation guidelines (24).

**Table 2 tab2:** HMA Acupuncture point grouping and functional classification.

Group	Acupuncture point	Code	Description
Central regulation	Baihui	GV20	At the intersection of the midline of the head and the line connecting the apexes of both ears.
	Shenting	GV24	0.5 cun directly above the midpoint of the anterior hairline.
	Yintang	GV29 (EX-HN3, also referred to as GV29)	At the glabella, the midpoint between the medial ends of the two eyebrows, on the anterior midline of the head.
Emotional modulation	Neiguan	PC6	2 cun above the transverse crease of the wrist, between the tendons of palmaris longus and flexor carpi radialis.
	Shenmen	HT7	At the ulnar end of the transverse crease of the wrist, in the depression on the radial side of the tendon of flexor carpi ulnaris.
	Sanyinjiao	SP6	3 cun directly above the tip of the medial malleolus, posterior to the medial border of the tibia.
Systemic support	Zusanli	ST36	3 cun below ST35, one finger breadth from the anterior crest of the tibia, in the tibialis anterior muscle.
	Hegu	LI4	On the dorsum of the hand, between the 1st and 2nd metacarpal bones, at the midpoint of the 2nd metacarpal bone on the radial side.
	Taichong	LR3	On the dorsum of the foot, in the depression distal to the junction of the first and second metatarsal bones, approximately 1.5 cun proximal to the web margin between the big toe and second toe.

This table presents the acupuncture points applied in HMA, categorized into functional domains including central regulation, emotional modulation, and systemic support. Each point is defined by its anatomical location and therapeutic relevance in TCM. Acupoints PC6, HT7, SP6, ST36, LI4, and LR3 are applied bilaterally, whereas GV20, GV24, and GV29 are applied on the midline.

**Table 3 tab3:** Characteristics of De Qi sensations and needling parameters.

Acupuncture point	De Qi sensation	Needling sensation description	Needling depth	Needling angle	Remarks
GV20	Aching, Numbness, Heaviness	Local soreness and spreading heaviness	10–20 mm	15–30°	
GV24	Aching, Numbness, Heaviness	Mild soreness radiating to the forehead	10–20 mm	15–30°	
GV29	Aching, Numbness, Heaviness	Subtle pressure and light tingling	5–10 mm	15–30°	
PC6	Aching, Numbness, Heaviness	Tingling and radiating sensation toward the hand	10–25 mm	45–90°	
HT7	Aching, Numbness, Heaviness	Soreness with calming dull sensation	5–15 mm	45–90°	
SP6	Aching, Numbness, Heaviness	Deep aching and mild distension	15–30 mm	45–90°	
ST36	Aching, Numbness, Heaviness	Heavy sensation spreading to the lower limb	20–30 mm	45–90°	
LI4	Aching, Numbness, Heaviness	Intense distending sensation radiating to fingers	10–20 mm	45–90°	
LR3	Aching, Numbness, Heaviness	Pressing pain and spreading warmth	15–25 mm	45–90°	

This table outlines the De Qi sensation characteristics, needling techniques, and clinical grouping of acupuncture points used in HMA for treating tobacco use disorder. The points are categorized into Central Regulation, Emotional Modulation, and Systemic Support groups based on their TCM functions.

**Figure 2 fig2:**
[figure not shown]
Anatomical Illustration of Acupuncture Points for the HMA Protocol. This diagram depicts the specific acupuncture points used in the HMA protocol, divided into three functional groups: Central Regulation (GV20, GV24, GV29), Emotional Modulation (PC6, HT7, SP6), and Systemic Support (ST36, LI4, LR3). These points target the neurological and psychological symptoms of TUD, aiming to regulate craving, emotional stability, and physical resilience during nicotine withdrawal.

#### Harmonizing mind acupuncture intervention

2.4.1

##### Rationale for acupuncture point selection

2.4.1.1

The HMA protocol comprises three functional acupuncture point groups—Central Regulation, Emotional Modulation, and Systemic Support—designed to address the multidimensional features of TUD. Compared with conventional approaches focusing on auricular or single-meridian strategies, HMA integrates classical meridian theory with neurofunctional principles.

The Central Regulation group (GV20, GV24, and GV29) is used to regulate cognitive and emotional functions. The Emotional Modulation group (PC6, HT7, and SP6) targets anxiety, mood disturbances, and sleep-related symptoms. The Systemic Support group (ST36, LI4, and LR3) is intended to enhance physiological regulation and alleviate somatic discomfort. Together, these point groups aim to address craving, emotional dysregulation, and physical symptoms associated with nicotine withdrawal.

##### Neurophysiological considerations

2.4.1.2

Emerging evidence suggests that acupuncture may modulate brain regions involved in addiction and emotional regulation, including the prefrontal cortex, amygdala, hippocampus, and nucleus accumbens (25, 26). These regions are implicated in craving, impulse control, and stress responses (27, 28). Acupuncture stimulation has also been associated with modulation of dopaminergic pathways and endogenous neurotransmitter release, which may contribute to the alleviation of withdrawal symptoms (29, 30).

##### Needling technique and safety

2.4.1.3

Sterile, single-use stainless steel needles (0.25 mm × 25 mm or 0.25 mm × 40 mm) will be inserted to depths of 10–20 mm, depending on anatomical location. Insertion angles will range from 15°–30° for cranial points and 45°–90° for limb points. Manual stimulation will be applied to elicit the De Qi sensation. Needles will be retained for 30 min, with stimulation applied every 10 min.

All procedures will follow standardized safety protocols. In the event of adverse reactions, treatment will be discontinued and managed appropriately by the attending acupuncturist.

#### Control intervention (nicotine replacement therapy)

2.4.2

Both groups will receive the same NRT regimen. Participants in the control group will receive NRT alone for 6 weeks.

The NRT regimen consists of transdermal nicotine patches administered at a fixed dose of 21 mg/day for the first 4 weeks, followed by 14 mg/day for weeks 5–6 (31). No dose adjustment based on VAS scores will be performed to avoid confounding feedback between the intervention and NRT dosage. All NRT doses will be recorded as administered and included as a covariate in sensitivity analyses.

#### Adherence monitoring and data collection

2.4.3

Participants will attend six in-person visits (baseline and Weeks 2, 4, 6, 10, and 24). Each visit will include:

(1) Compliance assessment: NRT patch verification and diary review (VAS scores and adverse events).(2) Outcome assessments (Table 1):

- CO and VAS: all visits.- PPA: Weeks 6 and 24.- SF-36, PSQI, BDI-II, and BAI: baseline and Weeks 4, 6, 10, and 24.

#### Behavioral counseling and attention control

2.4.4

All participants will receive standardized brief behavioral counseling (5–10 min per visit) based on the 5A model (Ask, Advise, Assess, Assist, Arrange), delivered by a trained research nurse. To balance clinical contact time between groups, participants in the NRT-only group will receive an additional 5–10 min of structured health education at each visit, matching the duration of acupuncture sessions in the intervention group. Health education topics are standardized and include general wellness, lifestyle modification, stress management, and smoking-related health risks, delivered using a predefined educational pamphlet to ensure consistency (24).

### Ethical considerations

2.5

To ensure participant welfare, individuals in the control group will be offered a complimentary six-week course of harmonizing mind acupuncture (HMA) after completion of the study, in accordance with Good Clinical Practice (GCP) guidelines (32).

### Outcomes

2.6

#### Co-primary outcomes

2.6.1

(1) Nicotine craving intensity will be assessed using a visual analog scale (VAS), consisting of a 100-mm horizontal line ranging from 0 (no craving) to 100 (maximum craving) (31). Participants will indicate their current level of craving by marking a point on the scale. The change in VAS score from baseline to week 6 serves as one of the co-primary outcomes.(2) Seven-day point prevalence abstinence (PPA) will be assessed at week 6. Self-reported abstinence over the preceding 7 days will be biochemically verified using exhaled carbon monoxide (CO). Participants with discordant self-reported and biochemical results (i.e., self-reported abstinence but CO ≥ 6 ppm) will be classified as non-abstinent (33). PPA at week 6 serves as the second co-primary outcome. PPA at week 24 will be analyzed as a secondary outcome.

VAS craving was selected as a co-primary endpoint due to clinical relevance and feasibility, while biochemically verified PPA provides an objective measure of cessation, together addressing both subjective withdrawal and confirmed abstinence (33).

